## Abstract

**Background:**

Pediatric obsessive-compulsive disorder (OCD) is a severely impairing disorder, associated with high levels of family accommodation (FA). Approximately 40 % of youth do not benefit from first-line treatment options (cognitive behavioral therapy or pharmacotherapy). Supportive Parenting for Anxious Childhood Emotions (SPACE) is a parent-based treatment, teaching parents to reduce FA and increase supportive parenting, thereby aiming to improve the child's OCD. This article presents the protocol of a multiple baseline single-case experimental design (SCED) study to test the efficacy of SPACE in reducing OCD severity and FA in youth with OCD.

**Methods:**

This SCED consists of a baseline, treatment, and follow-up phase. In total 25 youth (7–18 years) with OCD, who previously received cognitive behavioral therapy (CBT) unsuccessfully, aborted treatment early, or were not able to receive CBT due to too high levels of OCD/anxiety, and their parents will be included. They will be randomly allocated to one of three baseline phase options (4, 6 or 8 weeks). The treatment phase consists of 12 weekly sessions of SPACE with parents. Throughout all phases, OCD severity and FA will be briefly assessed thrice a week. Standard clinical measurements assessing OCD severity and FA and secondary parameters will be conducted at six timepoints, till 6 months follow-up.

**Conclusion:**

Combining the innovative SPACE treatment with a SCED provides detailed insight into the relationship between OCD and FA over time. Studying this in clinical practice in complex cases that are normally understudied, helps to improve more personalized care for youth with OCD.

## Background

1

Children and adolescents with obsessive-compulsive disorder (OCD) experience recurrent obsessions and compulsions causing significant impairments in their daily activities and family functioning. Obsessions are anxious or distress-provoking intrusive thoughts, images, or impulses. Compulsions are time-consuming ritualistic behaviors (e.g., repetitive checking, cleaning) or mental tasks (so-called cognitive compulsions, e.g., repeating sentences in one's head). OCD affects 0.5–2% of children [1,2] and is characterized by late recognition of symptoms, delayed start of treatment, and, if not treated, a chronic and disabling disease course that can disrupt development during childhood and adolescence [3].

Evidence-based first-line treatment options for pediatric OCD are cognitive behavioral therapy (CBT, including exposure and response prevention (ERP)) and pharmacotherapy (especially selective serotonin reuptake inhibitors; SSRI's). However, 40 % of children with OCD do not respond to these treatments [4,5] or drop out of treatment prematurely. In clinical trials 10 % of youth with OCD drop out of ERP treatment and 17 % drop out of pharmacotherapy [6]. In addition, little is known about treatment refusal rates in children with OCD, but it is common in clinical practice due to low motivation or high anxiety rates. Additional alternative treatment options for these unreached and often complex OCD cases are therefore urgently needed.

Increasing attention is being given to family factors that play a role in childhood anxiety and OCD [7,8], in particular to family accommodation (FA) [9,10]. FA encompasses behaviors of parents, siblings, and other caregivers to alleviate distress in the affected child. In families of children with OCD and other anxiety problems, FA is highly prevalent and significantly elevated compared with families of children without clinical anxiety disorders [11,12]. Higher FA is associated with greater severity of symptoms and poorer treatment outcomes in children and adolescents [13].

To improve treatment outcomes for children with OCD and anxiety, Lebowitz and colleagues [14] developed an innovative parent-based (stand-alone) treatment targeting FA in relation to children's anxiety and/or OCD: *Supportive Parenting for Anxious Childhood Emotions* (SPACE). A unique advantage of the program is that SPACE is a completely parent-based treatment protocol that can be applied without cooperation of the child, and thus can be used for families of children who are reluctant or not motivated to participate in treatment or do not respond sufficiently to CBT. Parents are taught to reduce FA and to increase supportive responses towards their child.

The theoretical foundation of SPACE is based on several perspectives, such as attachment theory [15], systemic therapy, CBT and Non-Violent Resistance (NVR) [16]. Attachment theory describes the mutually interactive bond between parents and children, in which parents are inclined to protect and respond to fear or distress cues of the child and the child largely depends on the parent in dangerous or stressful situations [15]. Anxiety activates this bond; the child seeks protection from the perceived danger and the parent provides protection and regulation. Within the SPACE framework, therefore, anxiety is considered as an interpersonal and systemic construct. Protective responses of parents to their child's OCD and anxiety can be considered as repeatedly activating the attachment system. Children with OCD and/or anxiety often have difficulties with self-regulating their emotions, which can be maintained by the protective responses of parents [17]. Then, within the family, a kind of maladaptive equilibrium may arise, in which the child relies on the repeated reassuring accommodation of parents. NVR provides a framework for altering this maladaptive equilibrium. The core principle of NVR is that in situations of conflict, productively acting relies on changing one's own behavior, and not focusing on changing the other's behavior. This can help parents to avoid being drawn into the child's demanding or coercive disruptive behavior dynamics that provoke family accommodations [18,19].

Empirical studies, primarily in the United States (US) have made clear that SPACE is promising. SPACE was evaluated in a non-inferiority randomized controlled trial (RCT), and found to be as efficacious as CBT in decreasing childhood anxiety and significantly more efficacious in decreasing FA [20]. More recently, both a low-intensity version of SPACE and the standard SPACE treatment protocol showed strong treatment effects for anxious youth, including OCD [21]. A case series showed that SPACE is a feasible and acceptable treatment option for parents of children with OCD [14]. However, SPACE has not been evaluated as rigorously outside the US and in youth with OCD. The current study aims to investigate the efficacy of SPACE on OCD severity and FA in Dutch youth with complex OCD, with a multiple baseline single-case experimental design (SCED). Secondly, we aim to identify predictors and moderators of treatment response (such as comorbidity, parental burden, and parental psychopathological symptoms) and gain more insight into the mechanisms of change. A major advantage of exploring an innovative parent-based treatment with a SCED is that this allows to gain more detailed insights into changes and barriers in the treatment over time in complex cases of youth with OCD.

## Design and methods

2

### Study design

2.1

This study uses a multiple baseline single-case experimental design (SCED) to examine the efficacy of the SPACE program in 25 children and adolescents and their families. A SCED uses a within-subject design to monitor in detail treatment effects on a case-by-case basis over time [22]. It is characterized by frequent repeated assessments of the individual's behavior across multiple phases with the intervention being absent and present. SCED is specifically suitable for innovative interventions for relatively small populations (such as youth with complex OCD) [[22], [23], [24]]. Importantly, using detailed, repeatedly measured data of participants, SCED's have sufficient statistical rigor comparable to larger group-based designs. With these characteristics, SCED's help to bridge the gap between science and practice [[25], [26], [27]].

The course of this study follows a multiple baseline design with three phases: the baseline phase (A, no treatment), treatment phase (B, treatment) and follow-up phase (C, no treatment). To assess primary outcomes, participants complete frequent brief assessments on OCD severity and FA thrice a week throughout all phases, resulting in 72 time points assessing OCD and FA, for SCED analyses. The treatment phase will be split up in two distinct phases: B1 and B2. The division in phases is made at the time parents implement their first plan to reduce a target accommodation (see *2.5. Intervention)*. We aim to explore whether the moment of implementation (start of phase B2) brings a major change in accommodation behavior and whether the actual implementation can be seen as a core working mechanism of SPACE. B1 includes the SPACE sessions before parents implement their plan and are dedicated to psychoeducation, increasing supportive responses, charting accommodations, choosing target behaviors, and formulating a plan. Implementation of the plan is not fixed to a certain treatment session, so the transition between B1 and B2 can alternate between participants, indicating the suitability of the SCED approach. It has been shown that including six participants in a SCED design is considered satisfactory to observe moderate treatment effects [28]. At least nine case series demonstrating efficacy are needed to consider an intervention as well established [29]. Based on previous studies investigating SPACE in children with anxiety and OCD, we expect 16–25 % to drop out of the SPACE treatment [20,30]. Therefore, this study aims to provide the SPACE intervention to 25 families and analyze all data conform the A-B1-B2-C design.

Additionally to the SCED design, comprehensive standard clinical assessments are carried out to assess for pre-, during-, post- and follow-up differences at the following six timepoints: T0: baseline assessment during intake; T1: at the end of the baseline phase (four, six or eight weeks after T0), before treatment starts; T2: after four treatment sessions (on average four weeks after T1); T3: after eight treatment sessions (on average eight weeks after T1); T4: after all 12 treatment sessions are completed (on average 12 weeks after T1); T5: follow-up assessment, six months after T0. Moreover, every treatment session parents report about their well-being and working alliance and the therapist report about illness severity and improvement. An overview of all assessments is provided in Fig. 1 and Table 1.

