### Randomization

2.4

Participants will be randomly allocated to a baseline length of four, six or eight weeks, to ensure internal validity [33]. Permuted block randomization will be used with blocks of 3 and 6 and be computerized (by the data collection system Castor EDC). It is not possible to blind the researcher conducting the assessments, since the following assessments (T1 – T5, see Fig. 1) depend on the baseline period that is randomly selected. All questionnaires will be completed online to reduce researcher influence.

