### Plan of statistical analysis for the SCED primary study parameters

3.1

In this study, the main objective is to explore the efficacy of SPACE. The primary analysis focuses on the change in the frequent measure on OCD and FA between baseline phase (A) and treatment phase (B1+B2). First, individual participants data will be separately systematically visually analyzed [61]. Next, individual data will and modelled using a generalized least squares (GLS) approach (assuming autocorrelation) [62]. To test the treatment effect on group level, a multilevel modelling approach [63] based on the examples of Shadish and colleagues (2013) [64] and Moeyaert and colleagues [63,65,66] will be used. Data from all individual participants will be included in the multilevel model and structured across a hierarchical three-level structure. Level 1 represents the frequent measurement occasions, with measures being nested within each participant. Level 2 represents the individual participants (mothers, fathers and children), with family members being nested in a family unit. Level 3 represents the family units (e.g. members of one family) included in this study. Adding time-variant predictors (the number of measurement occasion to model general time trend, a dummy-coded variable (0–1) representing the phase and an interaction term between these two) at Level 1 allows to explore for a shift in level of OCD and FA at the start of the treatment phase and the shift in trend during the treatment phase [65]. Multiple plausible multilevel models will be estimated to enhance conclusions about the treatment effect [63]. For these analyses a significance level of 0.05 is used.

Exploratory, we expect the greatest shift in OCD severity and FA level in phase B2 when parents implement their plan to reduce FA. By starting phase B2 directly after implementation of the plan we aim to explore the immediate effect of the implementation and shift in OCD and FA level during the second half of the treatment. For this purpose, an additional time predictor at Level 1 will be added to estimate shift in level and shift in trend for phase B2.

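### The exploratory B2 terms rest on linear time only, so a shared delayed or non-linear response can look like an effect of implementing the plan; adding a model with treatment-week terms and a caveat on mechanism is a cheap improvement

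*Protocol article*

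**What the plan says.** Under Randomization, the only thing allocated by chance is baseline length: "Participants will be randomly allocated to a baseline length of four, six or eight weeks, to ensure internal validity". That fixes when treatment starts.

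Under Study design, the boundary between B1 and B2 is set differently: "The division in phases is made at the time parents implement their first plan to reduce a target accommodation". Its timing is left to the family: "Implementation of the plan is not fixed to a certain treatment session, so the transition between B1 and B2 can alternate between participants". The stated purpose is to explore "whether the actual implementation can be seen as a core working mechanism of SPACE". In Table 1 implementation is the sixth of nine core components, after psychoeducation, supportive responses, charting, target choice and planning.

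Section 3.1 labels the analysis exploratory but gives it a direction: "Exploratory, we expect the greatest shift in OCD severity and FA level in phase B2 when parents implement their plan to reduce FA". It continues: "we aim to explore the immediate effect of the implementation and shift in OCD and FA level during the second half of the treatment". The base model has measurement occasion as a general time trend, a phase dummy and their interaction. For B2, a shift in level and a shift in trend are added.

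**The concern.** A multiple-baseline design draws its strength from switch dates set by chance. Randomised baselines protect the start of treatment, but the B1-to-B2 switch follows each family's own pace and comes after a fixed run of earlier components. Variation in that date is not the staggering that randomisation provides.

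The time terms already in the model are straight lines. If the true course bends during treatment, for example because the response to the B1 content is delayed, the bend has nowhere to go except into the B2 level or trend term. The result would read as an immediate effect of implementation although implementation did nothing. Mechanisms of change are a stated secondary aim, so a significant B2 shift could be given weight that the contrast does not carry.

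**Working it through.** **Counts.** Three prompts a week and 72 in total imply 72 / 3 = 24 weeks. Baseline has 4, 6 or 8 weeks x 3 = 12, 18 or 24 prompts. Treatment has 12 x 3 = 36. Follow-up has 72 - 36 - (12, 18 or 24) = 24, 18 or 12. These agree with the Assessments section. The article gives no sample-size figure for the B2 test, so there is none to reproduce.

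**Model as described in section 3.1.** For occasion t, treatment start a and implementation date s of a family:

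y = b0 + b1 t + b2 B + b3 B (t - a) + b4 B2 + b5 B2 (t - s) + error

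Here b4 is the B2 level shift and b5 the B2 trend shift.

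**Simulation with no implementation effect.** From the protocol: baselines of 4, 6 or 8 weeks, 36 treatment prompts, alpha 0.05, and 25 families with 16-25% dropout, so 25 x 0.84 = 21 to 25 x 0.75 = 18.75 completers; 20 were used. Assumed: one series per family, within-person SD 1.5 on the 0-10 item, lag-1 autocorrelation 0.3, mean improvement of about 2 points, two-sided testing, and the implementation sessions shown. Each case was fitted by GLS with AR(1) errors and the mean coefficient tested across cases, as a two-stage stand-in for the multilevel model (400 runs per cell). Cells show the rejection rate, with the mean coefficient in brackets where it matters.

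| True course | Term | Sessions 6-7 | Sessions 5-8 | Sessions 3-11 |
|---|---|---|---|---|
| Linear | level | 0.05 | 0.07 | 0.06 |
| Linear | trend | 0.03 | 0.03 | 0.04 |
| S-shape at week 6 | level | 0.65 (-0.70) | 0.54 (-0.61) | 0.13 (-0.27) |
| Slower S-shape | level | 0.24 (-0.35) | 0.18 (-0.31) | 0.09 (-0.18) |
| Starts at week 6 | trend | 0.96 (-0.34/week) | 0.89 (-0.32/week) | 0.54 (-0.32/week) |
| Early, decelerating | trend | 0.69 (+0.23/week) | 0.62 (+0.23/week) | 0.33 (+0.24/week) |

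A separate set of runs with no true effect gave level shifts of -0.33 to -0.70 with 21-68% rejections for sessions 5-8, and -0.18 to -0.38 with 6-26% for sessions 3-11.

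**With common treatment-week terms, both B2 terms kept.** The false level shift fell to about 0, with 6-10% rejections. A true 1-point step was recovered as 1.0. Power was about 85%, against 95-100% for the linear-trend model. That higher figure is partly bias: in similar runs the linear-trend model estimated a true 1-point step as 1.29-1.45.

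**Why the B2 trend must stay.** With week terms and a B2 level dummy alone, a true gradual effect of -0.3 per week with no step came out as +0.08, with 6% rejections.

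**When timing follows the family's own progress.** If each family's improvement centres on its own implementation date but is not caused by implementation, the week-term model still gave -0.90 with 83% rejections.

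**The case against.** The protocol does not claim that B2 will prove a mechanism. It says explore throughout, labels the analysis exploratory, plans visual and per-case GLS analysis and several plausible multilevel models, and for mechanisms adds cross-lagged correlations and single-case mediation analysis. All of that stands and limits the weight of the point, although those mechanism analyses also rest on unrandomised timing.

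Three stronger readings are tempting and are not supported:

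- *Any mid-course improvement would appear as an implementation effect.* Linear improvement is absorbed by the existing terms (3-7% rejections), and an early, decelerating response moves the B2 trend the opposite way.
- *Nearly every family implements mid-treatment.* The component order and the reference to the second half of treatment suggest it, but components are not sessions, no distribution is given, and the protocol says that timing varies. Wider spread shrinks the artefact.
- *Week terms would make the B2 shift causal.* They remove only a curve that families share by treatment week.

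It can also be said that the coding of an exploratory model belongs in a fuller plan. But the article itself states the B2 terms and the question that they are meant to answer, so a comment on that pairing is fair.

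**Conclusion.** The point holds as a cheap improvement. The exploratory B2 terms can mistake a shared delayed or otherwise non-linear response for an effect of implementation. Under the assumed S-shaped courses the false level shift is about 0.2 to 0.7 points on the 0-10 item, with false-positive rates from near 10% when implementation dates are widely spread to about 65% when they cluster. For improvement that begins mid-course, the false trend shift is significant in 54-96% of trials. These rates depend on the assumed curve, variance and spread of dates, none of which the protocol gives; the pattern is the finding, not the exact values. A reader might infer that the trial's main result is compromised. It is not: the primary test compares A with B1+B2 and does not use the implementation date. What does not follow from a B2 shift alone is that implementation is a core working mechanism.

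**What to change.** In section 3.1, include among the several plausible multilevel models a B2 model with treatment-week terms common to all families (weeks since session 1, categorical or smooth). Keep both the B2 level and the B2 trend term, and report the model beside the linear-trend version. Families that have not yet implemented stay in B1 as comparison time.

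In section 2.1, state that a B2 shift is a hypothesis-generating, within-treatment association with unrandomised timing. State also that week terms do not remove confounding if families implement when they are already improving, so the shift cannot by itself show that implementation is a core working mechanism.

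No new data are needed; the cost is one extra model, a few sentences, and a wider interval for the B2 shift. In simulation, power for a 1-point step falls from about 95% to about 85%. With noisier data it is lower: 56% with SD 2 and autocorrelation 0.6, in separate runs of a week-term model.

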**Fig. 1 fig1:**
[figure not shown]
Overview patient procedures and randomization SCED.

**Table 1 tbl1:** Core components and additional modules of the SPACE treatment.

	Component	Content
	*Core component sequence*	
1	Introduction	Setting the stage. Parents are introduced to the main aim of the SPACE program and receive psychoeducation about anxiety and/or OCD and their involvement in their child's behavior.
2	Increasing supportive responses	Parents explore how they tend to respond to the child's anxiety/OCD, are taught the concept of supportive responses and practice supportive statements.
3	Charting Accommodation	Parents learn to recognize their own accommodation behaviors and are asked to chart their accommodations in a dairy.
4	Choosing Target	Parents choose an accommodation behavior they want to reduce and set this target as a treatment goal.
5	Formulating Plan	Parents work with the therapist on a detailed plan how to implement a change in their target accommodation. Parents learn how they can inform their child, making a so-called announcement in the form of a letter to their child.
6	Implementation	Parents implement their plan and discuss progress with the therapist during the sessions.
7	Choosing Additional Target	Parents choose a second accommodation behavior to reduce and discuss the plan with the therapist.
8	Implementation of second target	Parents implement their plan to reduce the second target and discuss progress with the therapist during the sessions.
9	Summery and Termination	Parents review the progress this with the therapist. Any unclarities are resolved and the therapist discusses how parents can sustain their behavioral change.

	*Additional modules*	
1	Teaching and modelling self-regulation	Parents learn self-regulation skills to better cope with the child's distress. For example, relaxing breathing, muscle relaxation, cognitive restructuring, and self-talk.
2	Coping with disruptive behavior	Equip parents with tools to cope with disruptive or aggressive episodes of the child with NVR techniques (e.g., teaching parents to delay their response, utilize supporters, convey the severity of the child's behavior without being accusatory.
3	Coping with treats to self	Parents learn to respond appropriately when a child express treats to self by not ignoring the threat and not allowing the threat to undermine their determination to overcome the child's OCD.
4	Accessing support	Encouragement to enlist supporters from outside to bolster the parents and child in dealing with difficult processes.
5	Improving collaboration between parents	Integration of both parents' point of view and emphasizing supporting the child requires both empathic acceptance and reducing accommodation. In this module exercises as role play are used.

